## Abstract

Sucralose stands as the most common non-nutritive sweetener; however, its metabolic effects have sparked significant controversy over the years. We aim to examine the effects of sucralose daily intake on glycemia, subjective appetite, and gut microbiota (GM) changes in subjects with overweight or obesity. In this randomized, crossover, and controlled trial, 23 participants with a body mass index between 25 kg/m^2^ and 39.9 kg/m^2^ will be assigned to one of two interventions to receive either sucralose (2 mg/kg/day equivalent to 40% of the acceptable daily intake) or glucose (control) for 4 weeks, each phase separated by a 4-week washout period. The glycemic response will be determined during a meal tolerance test, subjective appetite will be evaluated using a visual analog scale, and GM changes will be analyzed by next-generation sequencing of the bacterial rRNA 16S gene from fecal samples. All measures will be performed before and after intervention periods. We hypothesize that sucralose supplementation induces changes in glycemic response, subjective appetite, and gut microbiota in overweight and obese participants. This protocol was approved by the Ethics Committee of the UJAT (No. 0721) and was registered in the Australian New Zealand Clinical Trials Registry (ACTRN12621001531808).

## 1. Introduction

Global obesity and overweight rates have risen sharply, becoming a major health concern due to their association with type 2 diabetes (T2D) and cardiovascular disease. Mexico ranks second in obesity prevalence among the nations belonging to the Organization for Economic Cooperation and Development (OECD), with 36.9% of its population affected [1]. Non-nutritive sweeteners (NNS) have been implemented as substitutes for sugar to reduce caloric intake and prevent body weight gain. NNS can be artificially produced as sucralose, aspartame, acesulfame K, or saccharin or can be obtained from natural sources, such as steviol glycosides or monk fruit [2].

Sucralose is an artificial NNS derived from sucrose, which has a sweetening capacity 600 times greater than sucrose and has an acceptable daily intake (ADI) estimated value of 5 mg/kg/day according to the Food and Drug Administration (FDA) [3]. The use of sucralose is widely recommended among individuals with obesity and T2D. However, experimental and clinical trials have reported undesirable effects on glucose and energy metabolism, which can be attributed to three potential mechanisms: activation of T1R2/T1R3 sweet taste receptors, affecting insulin and incretin release; triggering a cephalic response that may increase caloric intake; and interaction with gut microbiota (GM), potentially causing dysbiosis. In the latter case, sucralose may disrupt GM composition, increasing intestinal permeability and allowing lipopolysaccharides (LPS) to enter the bloodstream, leading to a low-grade inflammatory response (metabolic endotoxemia) that could induce insulin resistance [4].

In humans, the effects of realistic doses of sucralose on glucose metabolism have been mostly assessed in healthy subjects. Suez et al. showed a clear alteration in glycemic response after two weeks of consuming sucralose (1.8 mg/kg BW/day equivalent to 34% ADI, FDA), which was correlated with GM alterations [5]. Romo-Romo et al. reported an increase in insulin resistance estimated by the HOMA-IR index after only two weeks of sucralose consumption (2.25 mg/kg BW/day equivalent to 45% ADI, FDA) [6]. Recently, Mendez-García et al. (2022) found an altered glycemic response related to changes in GM composition after sucralose intake (0.65 mg/kg BW/day equivalent to 13% ADI, FDA) for 10 weeks [7]. Conversely, other studies in humans do not identify the harmful effects of sucralose on glycemic response or GM [2,8,9]. Thus, it is unclear whether sucralose can induce metabolic alterations modulated by the microbiota modifications.

Particularly, most previous studies examining glycemic response and appetite modifications to sucralose administration have been largely limited to studies in animal models or individuals with normal body weight [10,11,12,13,14,15,16,17]. However, subjects with increased body weight represent an important group due to their increased risk of developing metabolic diseases such as diabetes, hypertension, and heart disease. For this reason, we will conduct a crossover, randomized, and controlled study in subjects with overweight or obesity. The primary outcome of the study will be the glycemic and insulinemic responses, and the secondary outcomes will include pre-post intervention changes in fasting parameters of glucose, insulin, total cholesterol (TC), high-density lipoprotein cholesterol (HDL-C), and triglycerides. Additionally, pre-post changes in anthropometric measures, blood pressure, GM composition, and subjective appetite will be considered. The knowledge gained in this study about the potential metabolic alterations induced by sucralose will be crucial in guiding recommendations for its use, especially given its widespread presence in the food industry.

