## 2. Experimental Design

### 2.1. Participants

A total of 23 adults of both sexes will be recruited. During the screening process, subjects will assist with an interview with a healthcare provider to determine anthropometric indexes, blood pressure, fasting glucose determination, and medical check-ups. Participants will fulfill the following inclusion criteria: both genders, aged 18 to 50, overweight or obese (25–39.9 kg/m^2^), with fasting glucose < 125 mg/dl, and with a maintained stable weight in the previous three months. Patients receiving antibiotics, probiotics, or prebiotics without the ability to give informed consent, pregnant or breastfeeding women, smokers, or alcoholics who have allergies to sucralose or food intolerance, and those with heart, liver, gastrointestinal, or renal disorders will not be included. Patients who have sensitivity or discomfort related to the high sweetness of the test beverage and patients who need to receive treatments with antibiotics, probiotics, or other treatments with drugs that interfere with carbohydrate metabolism or microbiota integrity during the experimental period will be excluded.

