### 3.6. Statistical Analysis

Sample size calculation was performed using NCSS and PASS v. 11.0 software. To detect a difference of 10% in the primary outcome variable (glycemic response AUC) and considering a power of 80% and a type 1 error of 5% in a crossover design, a sample size of 19 participants was calculated. However, to allow for a dropout rate of 20%, 24 participants will be considered. Four samples per participant will be analyzed: two baselines and two endpoints. The primary analysis will be performed using GraphPad Prism v. 7.0 and QIIME Software. The D’Agostino and Pearson tests will be used to determine Gaussian distributions. Differences in fasting biochemical markers will be assessed using a one-way analysis of variance (ANOVA) in combination with Tukey’s post hoc test. Time-course data will be analyzed by two-way repeated measures (RM) ANOVA to assess the effects of treatment, time, and the interaction of treatment and time. The intervention´s effect on GM community dissimilarity will be analyzed with permutational multivariate analysis of variance (PERMANOVA) on the Bray–Curtis distance and visualized with Principal Component Analysis (PCoA). ANOVA, or the Kruskal–Wallis test, will be used to compare alpha diversity using the Shannon index. The Firmicutes/Bacteroidetes ratio (F/B ratio) will be calculated from relative abundances. A *p*-value < 0.05 will be considered significant for all analyses.

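### The Introduction names two primary outcomes and section 3.6 names one, with no joint decision rule; the stated 5% error and 80% power hold together only if glycemic AUC is the sole primary

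*Protocol article*

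**What the plan says.** The Introduction defines the primary outcome as two responses: "The primary outcome of the study will be the glycemic and insulinemic responses". Section 2.3 shows that these are separate measurements, since glucose and insulin are both assayed in the blood samples of the 2-hour meal tolerance test.

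Section 3.6 works with one variable: "To detect a difference of 10% in the primary outcome variable (glycemic response AUC"), "considering a power of 80% and a type 1 error of 5% in a crossover design", from which "a sample size of 19 participants was calculated". After the dropout allowance, "to allow for a dropout rate of 20%, 24 participants will be considered". Insulin plays no part in the calculation.

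The same section ends with one significance threshold, p below 0.05, which "will be considered significant for all analyses". For time-course data it plans a two-way repeated measures ANOVA with treatment, time and interaction effects and does not say which effect decides. No test of the AUC is named. Tukey's procedure is the only multiplicity adjustment mentioned, and it is assigned to the fasting markers, which are secondary.

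The hypothesis in the Abstract does not settle the matter. It names glycemic response, appetite and gut microbiota, and leaves out insulin.

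**The concern.** A trial with one primary variable tested at 5% has a 5% chance of a false positive primary result. A trial with two primary variables needs a rule that combines them, and the rule determines which design figure suffers. If either response may carry the claim, the type I error rises. If both must be significant, the power falls. The article gives two definitions of the primary outcome and no rule.

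As the text stands, a significant insulin response with a null glucose AUC could be reported as a positive primary result on the Introduction, or as a negative trial on section 3.6. The reverse pattern is open to the same choice. The Introduction says the results should guide recommendations on sucralose use, so what counts as a positive trial should be fixed in advance.

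**Working it through.** **Inputs.** From section 3.6: 5% type I error (taken as two-sided; the article does not say), 80% power, a 10% difference in glycemic AUC, 19 evaluable, 20% dropout, 24 in total. Not given, and therefore assumed: the correlation between the glucose and insulin tests (range 0 to 0.9), and the effect size and power for insulin (set equal to glucose).

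**1. The plan's own figures.** The dropout step reproduces: 19 / (1 − 0.20) = 23.75, rounded up to 24. The 19 cannot be reproduced, because no mean, SD or within-subject CV is stated. Solving backwards with a paired t-test (noncentral t, two-sided 0.05, 80% power), n = 19 implies a standardized difference of about 0.68 to 0.70. That is an SD of the paired differences of about 14.3% to 14.7% of the mean (10 / 0.701 to 10 / 0.680).

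**2. Glycemic AUC is the sole primary.** One test at 0.05 and 80% power. Both stated figures hold as written.

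**3. Either response suffices, each at 0.05.** If independent, the family-wise error is 1 − 0.95² = 0.0975. For correlated tests it is 1 − P(|Z₁| < 1.96 and |Z₂| < 1.96) under a bivariate normal distribution.

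**4. Both responses required.** Type I error is held at 5%. If independent, joint power is 0.80 × 0.80 = 0.64. For correlated tests it is P(Z₁ < 0.842 and Z₂ < 0.842), where 0.842 is the normal quantile for 80%.

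| Assumed correlation | Family-wise error, either suffices | Joint power, both required |
|---|---|---|
| 0 | 9.75% | 64% |
| 0.5 | 9.1% | 69% |
| 0.7 | 8.3% | 71% |
| 0.9 | 7.0% | 75% |

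Joint power cannot exceed the power of the weaker test, so with glucose at 80% it cannot pass 80%. If insulin has less than 80% power, the joint figures fall below those shown.

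**5. Cost of keeping two primaries with a split alpha.** At 0.025 each with 19 evaluable, and the standardized difference from step 1, power per outcome is about 69% to 72%. Restoring 80% takes 22 to 24 evaluable, or 28 to 30 recruited (22 / 0.8 = 27.5, rounded up; 24 / 0.8 = 30). For insulin this again borrows the glucose effect size.

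**The case against.** The strongest reply is that the 5% and 80% in section 3.6 are stated for glycemic AUC alone and are not wrong for that variable. The article never writes that success on either response is enough. Section 3.6, read alone, describes a trial with one primary outcome and no inflation between the two responses. This stands: the error inflation belongs to one reading of the text. A reader might infer that the 5% level is definitely not held, but the documents do not support that. What they show is an undefined decision rule.

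A second reply is that a condensed article leaves multiplicity to a full protocol or analysis plan. That holds for details such as false-discovery control among secondary outcomes, where nominal p-values are common practice. It does not hold for which outcome is primary, which the article states in two ways, nor for the uniform 0.05 threshold, which it fixes itself. Tukey's test does not help, because it compares within each fasting marker and not across the two responses.

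A reader might also infer from the uniform threshold that a false positive among the secondary outcomes is more likely than not. Counting about 21 non-primary outcomes gives 1 − 0.95²¹ = 66%, but only if they are independent. They are not: HOMA-IR is computed from fasting glucose and insulin, and BMI from weight. The figure is an upper bound for positively correlated outcomes, and the documents do not show that the true value exceeds one half.

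**Conclusion.** The point holds as a contradiction about the primary outcome with no rule to resolve it. Of the three readings open, only one, glycemic AUC as sole primary, keeps both stated design figures, and the Introduction contradicts it. The other two cost either about 2 to 5 percentage points of type I error (7.0% to 9.8% against 5%) or about 5 to 16 points of power (64% to 75% against 80%). Those sizes rest on an assumed correlation of 0 to 0.9 and, for power, on an assumed 80% for insulin. The contradiction itself needs no assumption. It should be corrected, and the trial remains interpretable once it is.

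**What to change.** Before outcome data are analysed, issue a dated amendment and update the registry entry so that the Introduction and section 3.6 agree:

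- Name glycemic AUC 0-120 minutes as the single primary outcome, and the sucralose-versus-glucose comparison of that AUC as the one deciding test at 5%. The test must be named, because section 3.6 gives only a time-course ANOVA with three effects; naming the variable alone would leave the primary error rate undefined.
- Make insulin AUC the first secondary outcome, tested at 5% only if the glycemic AUC test is significant.
- Limit the confirmatory 0.05 rule to this sequence, and label p-values for all other outcomes nominal or exploratory. False-discovery control within the appetite or microbiota outcomes is optional.

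The sample size stays at 19 evaluable and 24 with dropout, and glycemic AUC gives up no alpha. The price is that insulin loses stand-alone primary status. Section 3.3 says recruitment began in September 2023 and section 3.1 says the trial is registered, so the change needs a recorded date and reason. If the sponsor prefers to keep both responses as primary, the article must state the joint rule or alpha split and re-size the trial with an insulin effect size.

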### 3.2. Trial Design

This study is a crossover, randomized controlled trial (RCT) to determine the effect of daily intake of sucralose on glycemic response, subjective appetite, and GM in subjects with overweight or obesity. Participants will be invited to attend the laboratory for preliminary measurements and baseline data after providing written informed consent. Following this, they will be randomly allocated into one of two treatment groups to receive either sucralose or glucose (control) daily for four weeks, each phase separated by a four-week washout period. An MTT, subjective appetite assessment, and stool collection will be carried out before and after each intervention phase (four measurement points). A flow diagram of the study protocol is shown in Figure 1, and the participant timeline actions are presented in Table 1.

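### Secondary and further outcomes are worded as pre-post changes with no baseline adjustment named; an unadjusted change contrast can have up to about twice the variance of a baseline-adjusted one

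*Protocol article*

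**What the plan says.** The trial is a two-period crossover in which participants "receive either sucralose or glucose (control) daily for four weeks, each phase separated by a four-week washout period" (section 3.2).

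The Introduction sets out three tiers of outcome:
- **Primary:** "The primary outcome of the study will be the glycemic and insulinemic responses". This is not called a change. Section 3.6 names the primary variable as the AUC of the glycemic response.
- **Secondary:** "the secondary outcomes will include pre-post intervention changes in fasting parameters", meaning glucose, insulin, total cholesterol, HDL-C and triglycerides.
- **Further:** "pre-post changes in anthropometric measures, blood pressure, GM composition, and subjective appetite will be considered".

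A baseline exists in each phase. According to section 3.2 the assessments "will be carried out before and after each intervention phase (four measurement points"), Table 1 shows the same schedule, and section 3.6 adds: "Four samples per participant will be analyzed: two baselines and two endpoints".

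For analysis, section 3.6 names one-way ANOVA with Tukey's test for fasting markers, two-way repeated-measures ANOVA for time courses, ANOVA or Kruskal-Wallis for alpha diversity, and PERMANOVA for community dissimilarity. None of these is described with a phase baseline as covariate or with a period effect. Section 3.6 does not name a change score as the analysed variable either.

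**The concern.** Section 4 justifies the crossover by each participant serving as his own control. Comparing the two end-of-phase values within a person already achieves that. A comparison of two pre-post changes uses four measurements instead of two, and the two baselines bring their own day-to-day variation. Subtracting them helps only if a baseline says more about the endpoint of its own phase than about the person's general level.

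Using the baseline as a covariate lets the data decide how much of it to subtract. All four measurements are already planned, so the gain costs almost nothing to collect. What is at stake is the precision of the secondary and further continuous outcomes in a trial with about 19 evaluable participants.

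**Working it through.** **The plan's own figure.** Section 3.6 starts from these inputs: "To detect a difference of 10% in the primary outcome variable (glycemic response AUC"), then "considering a power of 80% and a type 1 error of 5% in a crossover design", giving 19. No SD or CV is stated, so 19 cannot be reproduced. Solved backwards (two-sided test assumed), it implies an SD of the within-person difference of about 14.7% of the mean by the t distribution, or 15.6% by the normal approximation. The dropout step does reproduce: 19/0.8 = 23.75, rounded up to 24.

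**Set-up.** For each person let D_post be the difference between the two end-of-phase values and D_base the difference between the two phase baselines. Assume both have variance V, with correlation r between them. Then:
- endpoints only: V
- change scores: Var(D_post − D_base) = V + V − 2rV = 2V(1 − r)
- baseline-adjusted: V(1 − r²)

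The large-sample ratio of change to adjusted is 2(1 − r)/[(1 − r)(1 + r)] = 2/(1 + r).

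Estimating the slope multiplies the adjusted variance by about 1 + 1/(n − 4). At n = 19 this is 1 + 1/15 = 1.067.

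| r (assumed) | Change, 2(1−r) | Adjusted, 1−r² | Ratio, large sample | Ratio ÷ 1.067 | Simulated, n=19 |
|---|---|---|---|---|---|
| 0 | 2.00 | 1.00 | 2.00 | 1.88 | 1.86 |
| 0.25 | 1.50 | 0.94 | 1.60 | 1.50 | 1.52 |
| 0.5 | 1.00 | 0.75 | 1.33 | 1.25 | 1.26 |
| 0.9 | 0.20 | 0.19 | 1.05 | 0.99 | about 0.98 |

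The simulations used a two-sequence crossover with period allowed for.

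**What r means.** If rw is the correlation of a baseline with the endpoint of its own phase, and rb the correlation across phases, then r = (rw − rb)/(1 − rb). With rb = 0.7 and rw = 0.7, 0.8 and 0.9, r is 0, 1/3 and 2/3. The large-sample ratios are 2.0, 1.5 and 1.2; simulation at n = 19 gave about 1.85, 1.42 and 1.12.

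**Two thresholds.** The change score beats the unadjusted endpoint contrast only when 2(1 − r) < 1, that is r > 0.5. Adjustment stops paying at n = 19 when 2/(1 + r) = 1.067, that is r ≈ 0.88.

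**The case against.** **Outcome wording is not an estimator.** The change wording stands in the Introduction, and section 3.6 never prescribes an unadjusted change-score contrast. A change analysed with the phase baseline as covariate gives the same treatment estimate as the adjusted endpoint. A condensed article may also leave the covariate list to a fuller document. This stands in part: the loss is conditional on the changes being compared without adjustment. The article does, however, fix the outcomes as changes and names tests that carry no baseline or period term, so the less efficient analysis is the natural reading.

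**The stated power.** A reader might infer that the 80% is missed. If 19 had been sized on an endpoint contrast and the AUC were then analysed as an unadjusted change, power would be 51%, 68% or 93% for same-phase correlations of 0.7, 0.8 and 0.9 with cross-phase correlation 0.7. The documents do not support that inference. The primary outcome is not defined as a change, the variance behind 19 is not stated, and the result runs from well below 80% to well above it.

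**Unequal baselines.** A reader might also infer bias, because phase II follows a washout while Table 1 shows no run-in before phase I. Sequence is randomised, so this is a period effect balanced across treatments. It argues for a period term and does not make change scores invalid.

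**Small samples.** Adjustment is not guaranteed to win at n = 19: above r of about 0.88 the cost of the slope slightly exceeds the gain. This stands, but the possible loss is bounded at about 7%, against a possible near-doubling of variance the other way.

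**Conclusion.** The point holds for the continuous secondary and further outcomes, as a matter of efficiency. Change from phase baseline is an unbiased outcome in a randomised crossover, but an unadjusted contrast of changes can carry up to about twice the variance of the adjusted contrast: about 1.86 times at r = 0, 1.26 at r = 0.5 and roughly equal at r = 0.9, with 19 evaluable participants. This rests on equal variances of the baseline and endpoint differences, on non-negative r, and on an assumed range for r, since the documents give no correlation. It does not extend to the sample size justification for the AUC, nor to the PERMANOVA of community dissimilarity.

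**What to change.** For the continuous outcomes now worded as pre-post changes, state that inference rests on the sucralose-versus-glucose contrast of end-of-phase values, with period and the within-person baseline difference as covariates. Report the raw pre-post changes alongside. State that the primary AUC is compared in the same way, so that its definition and analysis are explicit.

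The cost is wording plus one covariate; no extra visit or sample is needed, because both baselines are already scheduled. The statistical price is one degree of freedom for the slope, about 7% in variance at n = 19, which can slightly outweigh the gain if r turns out very high.

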## 2. Experimental Design

### 2.1. Participants

A total of 23 adults of both sexes will be recruited. During the screening process, subjects will assist with an interview with a healthcare provider to determine anthropometric indexes, blood pressure, fasting glucose determination, and medical check-ups. Participants will fulfill the following inclusion criteria: both genders, aged 18 to 50, overweight or obese (25–39.9 kg/m^2^), with fasting glucose < 125 mg/dl, and with a maintained stable weight in the previous three months. Patients receiving antibiotics, probiotics, or prebiotics without the ability to give informed consent, pregnant or breastfeeding women, smokers, or alcoholics who have allergies to sucralose or food intolerance, and those with heart, liver, gastrointestinal, or renal disorders will not be included. Patients who have sensitivity or discomfort related to the high sweetness of the test beverage and patients who need to receive treatments with antibiotics, probiotics, or other treatments with drugs that interfere with carbohydrate metabolism or microbiota integrity during the experimental period will be excluded.

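### The Abstract and Section 2.1 plan for 23 participants, but Section 3.6 derives 24; at 23 the stated 20% dropout allowance is not quite met

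*Protocol article*

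**What the plan says.** The protocol article gives the planned number of participants in three places.

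- Abstract: "23 participants with a body mass index between 25 kg/m^2^ and 39.9 kg/m^2^ will be assigned to one of two interventions".
- Section 2.1 (Participants): "A total of 23 adults of both sexes will be recruited".
- Section 3.6 (Statistical Analysis): "a sample size of 19 participants was calculated", followed by the statement that "to allow for a dropout rate of 20%, 24 participants will be considered".

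The basis given for the 19 is "To detect a difference of 10% in the primary outcome variable (glycemic response AUC"), "considering a power of 80% and a type 1 error of 5% in a crossover design". Section 3.6 gives no standard deviation and does not say which test was used or whether it was two-sided.

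**The concern.** All three passages describe people entering the trial, before any losses. The 23 cannot be a count of completers, because Section 3.6 puts that number at 19. The planned sample size therefore has two values in current text.

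Two things are at stake. First, only one of the two numbers provides the dropout allowance that the plan says it makes. Second, the text does not say which number closes recruitment, which Section 3.3 says began in September 2023. If the final report shows 23 enrolled, a reader could not tell whether the target was met or missed by one.

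**Working it through.** **Inputs from the article.** Required number 19, dropout 20%, inflated number 24, power 80% and type 1 error 5% (all Section 3.6); planned number 23 (Abstract and Section 2.1).

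**1. Reproduce the plan's own figure.** Inflated number = required number / (1 − dropout) = 19 / (1 − 0.20) = 19 / 0.80 = 23.75, rounded up to 24. This matches Section 3.6 exactly.

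**2. Apply the same dropout rate to both numbers.** Expected completers = enrolled × (1 − dropout). Losses tolerated = enrolled − 19.

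| Enrolled | Expected completers | Against 19 | Losses that still leave 19 |
|---|---|---|---|
| 23 | 23 × 0.80 = 18.4 | 0.6 short | 4 (4/23 = 17.4%) |
| 24 | 24 × 0.80 = 19.2 | 0.2 over | 5 (5/24 = 20.8%) |

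At 23, a fifth loss leaves 18.

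**3. Chance of reaching 19 completers.** This takes dropout as independent between participants with probability 20% (an assumption) and uses the exact binomial tail.

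- P(at least 19 of 23 complete) = 0.501
- P(at least 19 of 24 complete) = 0.656

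**4. Effect on power if 18 complete.** The 19 cannot be reproduced without a standard deviation, so the standardized within-person difference has to be solved backwards. Assume a two-sided paired t-test at 5% with noncentral t power, and assume that 19 is the smallest whole number giving at least 80%. That fixes a range.

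| Case | Standardized difference | Implied SD of the within-person difference, as % of the mean AUC (10% / standardized difference) | Power at 19 | Power at 18 |
|---|---|---|---|---|
| 19 gives exactly 80% | 0.680 | 14.7% | 80.0% | 77.6% |
| Limit at which 18 would already suffice | 0.701 | 14.3% | 82.3% | 80.0% |

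Power at 18 completers therefore lies between about 77.6% and just under 80%. With n − 2 degrees of freedom, as in a two-period crossover analysis, the lower end is 77.5%.

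**The case against.** The strongest reply is that the gap is one participant and 0.6 of an expected completer, and that it touches no estimand, no analysis and no error rate. That is right about the size. Even 24 leaves about a one-in-three chance (1 − 0.656 = 0.344) of fewer than 19 completers, so moving from 23 to 24 improves the odds without securing the target. Section 3.6 also uses a looser verb for its 24 than Section 2.1 uses for its 23. None of this removes the contradiction: the article states two different numbers for the same quantity, and the 20% allowance fits only one of them. The missing analysis plan does not explain it either, since both numbers are printed in the article.

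A reader might infer more than the article supports in four ways.

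- **That the trial will finish below 19 completers.** The 18.4 is an expectation. With 23 enrolled the chance of at least 19 completers is about even, and four losses still leave 19.
- **That power falls to 77.6%.** This is the lower end of a range, and it holds only if 19 gives exactly 80%. The article supplies neither the standard deviation nor the test.
- **That 23 comes from a wrong inflation formula.** It is true that 19 × 1.20 = 22.8 rounds up to 23, but truncating 23.75 also gives 23, and a slip in editing would do so too. The only inflation the article shows is the correct one.
- **That 23 is a fault because it cannot be divided equally between the two sequences.** Section 3.3 describes an online random number generator and states neither blocking nor an equal split. Without such a restriction, 24 would not guarantee 12 per sequence. A 12 to 11 split costs very little precision.

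**Conclusion.** The point holds as a small but real contradiction. The Abstract and Section 2.1 give 23; Section 3.6 gives 24, and 24 is the number that follows from 19 completers and 20% dropout. At 23 the stated allowance falls short by 0.6 expected completers, and the tolerable loss is 17.4% instead of 20%.

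The shortfall itself rests only on the article's figures. The completion probabilities rest on independent 20% dropout. The power range rests on a two-sided paired t-test for which 19 is the smallest adequate number. On those assumptions the loss at 18 completers is at most about 2.4 points below the stated 80%. This is not a major power failure, but the planned sample size should be one number and should agree with its own derivation.

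**What to change.** State 24 in the Abstract and in Section 2.1, to match Section 3.6. This changes one number in two places and adds one participant, whom Section 3.6 already counts.

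If 23 is the real target, leave the Abstract and Section 2.1 as they are and correct Section 3.6 in one of two ways:

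- give the dropout allowance as about 17% (4 losses of 23), which keeps 19 completers; or
- keep 20% dropout and say that about 18 completers are expected, with power slightly below 80%, recomputed from the standard deviation used in the original calculation. The range above should not be copied in as the planned power, because it is solved backwards.

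Either route is a text correction and leaves the design and the analysis unchanged.
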